#### General Dose Reduction Guidelines

See Appendix 2

### Ribavirin Dose Modifications

If the ribavirin concentration measured on day 28 in Groups A and B is below the target concentration (2.5 mg/L (10.25 mol/L)), the dose of ribavirin should be increased as soon as possible preferably within 2 weeks of measuring the ribavirin concentration if the patient can tolerate an increase. The new recommended dose is the previously given dose divided by the concentration of ribavirin measured multiplied by the target concentration (2.5 mg/L (10.25 mol/L)) (see Appendix 3).In the event of a change in ribavirin dosing in Groups A (“Loading”) and B (“Priming”), a new local ribavirin concentration should be evaluated after 4 weeks. Ribavirin should be administered twice-daily with food.

Where dose reduction is required stepwise incremental adjustments of 200 mg (1 tablet) should be utilized where clinical circumstance allows.

If either of the following is confirmed, it is recommended that the ribavirin dose should be reduced, at the discretion of the investigator dependent on local treatment guidelines:

- A patient without significant cardiovascular disease experiences a fall in hemoglobin to <10 g/dL (<100 g/L) and >8.5 g/dL (>85 g/L) or
- A patient with stable cardiovascular disease experiences a fall in hemoglobin by >2 g/dL (>20 g/L) during any 4 weeks of treatment

For the purposes of this protocol, patients with “stable cardiovascular disease” include not only patients with known, stable cardiac and vascular disorders, but also patients with major cardiac risk factors including hypertension and diabetes mellitus.

Patients who have more than a 3 g/dL (30 g/L) decrease from baseline in their Hgb concentration should have an appropriate work-up for anemia, including reticulocyte count, search for sources of bleeding, etc.

Moreover, ribavirin should be discontinued under the following circumstances:

- If a patient without significant cardiovascular disease experiences a fall in hemoglobin confirmed to be less than 8.0 g/dL (80 g/L).
- If a patient with stable cardiovascular disease maintains a hemoglobin value <12 g/dL (<120 g/L) despite 4 weeks on a reduced dose of 600 mg.

Ribavirin monotherapy is not allowed; in the event that PEG-IFN alfa-2a treatment has to be permanently discontinued the patient must cease all study medications and must be followed for safety reasons for at least 12 weeks.

In the event of ribavirin being discontinued, the patient may continue to receive PEG-IFN alfa-2a monotherapy for the rest of the planned treatment period. Ribavirin can be reintroduced, at the investigator´s discretion. Ribavirin may be reintroduced at full dose or in a stepwise manner as indicated in the table above.

The use of erythropoietin (NeoRecormon) ≥3000 IE 3 times week sc is permitted throughout the study at the discretion of the treating physician with the exception if the patient has any of the following exclusion criteria for the use of erythropoietin: platelet count >500,000, risk of thrombosis, or poorly controlled hypertension, especially if hemoglobin decreases persistently to < 10.0 g/dL or in the event of a rapid decrease in hemoglobin exceeding 4.0 g/dL over a 2 week period. If erythropoietin is initiated, a new ribavirin concentration at local lab should be evaluated after 4 weeks in Groups A (“Loading”) and B (“Priming”).

In the event of anemia, dose reductions of ribavirin are permitted in all study arms throughout the study at the discretion of the treating physician.

If hemoglobin decreases to < 8.0 g/dL, ribavirin should be discontinued.

If hemoglobin decreases to < 7.0 g/dL, blood transfusion should be considered at the discretion of the treating physician.

If hemoglobin decreases to < 6.5 g/dL, blood transfusion should be given.

If any dose of ribavirin dosing is missed (or changed), that information must be recorded on the Case Report Form.

## Premature Withdrawal

Patients have the right to withdraw from the study at any time for any reason. The investigator also has the right to withdraw patients from the study if it is in the best interest of the patient, e.g. in the event of intercurrent illness, adverse events, insufficient therapeutic response, protocol violations, administrative reasons or other reasons. An excessive rate of withdrawals can render the study uninterpretable. Therefore, unnecessary withdrawal of subjects should be avoided. Should a subject decide to withdraw, all efforts will be made to complete and report the observations as thoroughly as possible.

The investigator should contact the subject either by telephone or through a personal visit. Alternatively a responsible relative must be contacted to determine as completely as possible the reason for the withdrawal. If the reason for removal of a subject from the study is an adverse event or an abnormal laboratory test result, the principal specific event or test will be recorded on the Case Report Form.

All patients who discontinue from treatment prematurely should be assessed at 12 weeks post their last dose of study medication for safety reasons (see Section 5.3.2).

Patients who discontinue from treatment prematurely after the first 12 treatment weeks and whose HCV RNA is undetectable at last PCR assessment are expected to return for PCR assessments at the end of treatment visit (i.e. as soon as possible after the last dose of study medication) and 24 weeks post end of treatment (see Section 5.3.1).

If necessary, patients may discontinue from ribavirin treatment and remain on PEG-IFN monotherapy. However, because no benefit has been shown from ribavirin monotherapy in the treatment of CHC, patients who discontinue from PEG-IFN must discontinue from the entire treatment regimen (PEG-IFN plus ribavirin).

## Warnings and Precautions

### Peginterferon-alpha-2a

Alpha interferons, including PEG-IFN may cause or aggravate fatal or life-threatening neuropsychiatric, autoimmune, ischemic, and infectious disorders. Patients should be monitored closely with periodic clinical and laboratory evaluations. Therapy should be withdrawn from patients with persistently severe or worsening signs or symptoms of these conditions. In many, but not all cases, these disorders resolve after stopping PEG-IFN therapy.

To date, no teratology or reproduction studies have been conducted in humans with PEG-IFN. Primate teratology studies indicate an increased incidence of spontaneously aborted fetuses in pregnant rhesus monkeys (*Macaca mulatta*) receiving high doses of intramuscular Roferon®-A. Studies with Roferon®-A in non-pregnant rhesus monkeys have shown menstrual cycle irregularities, including prolonged menstrual periods. Male fertility and teratological evaluations have yielded no significant adverse effects up to date. However, fertile men will be excluded from this study unless using effective contraception during the treatment period.

Interferons are human proteins with a substantial degree of species specificity making extrapolation of animal study data to humans of questionable value. Investigations have been conducted in normally cycling healthy women using non-recombinant human leukocyte interferon. Results demonstrate a significant reduction of serum estradiol and progesterone concentrations during the treatment interval.

There are no adequate, controlled studies of any IFN in pregnant women.

Please refer to the Investigator´s Brochure (8) for further information.

### Ribavirin

Ribavirin is a known teratogen (see below for further information). **Therefore, extreme care must be taken to avoid pregnancy during the study in female patients, and female partners of male patients. RIBAVIRIN THERAPY SHOULD NOT BE INITIATED UNLESS A REPORT OF A NEGATIVE PREGNANCY TEST HAS BEEN OBTAINED IMMEDIATELY PRIOR TO INITIATION OF THERAPY.**

Fertile patients will be excluded from this study unless they are using two reliable forms of contraception during the treatment period and follow-up. Females who are pregnant or lactating will also be excluded. A pregnancy test will be performed on each female of childbearing potential prior to entry into the study and must be performed at study visits thereafter during the study. Moreover, fertile females and males should continue to use effective birth control (and fertile females to perform a monthly urine pregnancy test) for 6 months following their last dose of ribavirin.

#### Pregnancy

Ribavirin has a significant teratogenic and/or embryocidal potential in all test animals. These effects were observed even at doses as low as one twentieth of the recommended human dose. Malformations of the skull, palate, eye, jaw, limbs, skeleton, and GI tract were observed; the incidence and severity of teratogenic effects increasing with escalation of the drug dose. Survival of fetuses and offspring was reduced. In conventional embryotoxicity and teratogenicity studies in rats and rabbits, no effect dose levels were well below those for proposed clinical use.

Therefore, in order to avoid pregnancy, females of childbearing age and males should use two reliable forms of effective contraception (combined) throughout the entire period of the study (treatment and follow-up): these may include, but are not limited to, birth control pills, IUDs, condoms, diaphragms, implants, surgical sterilization, or being in a post-menopausal state.

It should also be noted that ribavirin accumulates in spermatozoa (19), i.e. concentrates in the semen. Because ribavirin may be transmitted in semen, it is recommended that one method of contraception be a barrier-type, e.g., condom.

If pregnancy occurs in a patient or partner of a patient during the treatment period, the cases should be handled as described in Section 8.2.4 (“Pregnancy”).

Also, a male patient must immediately report to the investigator any existing or occurring pregnancy in a sexual partner (even if he did not father the child) that occur while he is taking study medication and for 7 months following discontinuation of study medication. Such male patients must not continue to receive ribavirin, which accumulates in spermatozoa. The latter reason also leads to the recommendation of using a contraceptive barrier method in addition to another contraceptive. The partner should be counseled and followed as described above. The male patient will be discontinued from ribavirin (and can continue to receive PEG-IFN) and followed per the provisions of the protocol.

The patient consent form has to include this information with special attention to the potential risk to the fetus should conception occur while the patient or sexual partner is participating in PEG-IFN/IFN and ribavirin trials.

#### Carcinogenesis and Mutagenesis:

Although the literature and sponsor-conducted studies indicate that ribavirin is genotoxic (20), results from the 6-month carcinogenicity study in p53 (+/-) knockout mice revealed no evidence of treatment-related neoplasia. A study in rats to assess the carcinogenic potential of ribavirin is ongoing.

#### Adverse Reaction

The primary toxicity of ribavirin is anemia. Reduction in hemoglobin levels generally occurs within the first 1-2 weeks of initiating therapy. Cardiac and pulmonary events associated with anemia may occur.

Ribavirin should be administered with caution to patients with pre-existing cardiac disease. Patients should be assessed before commencement of therapy and should be appropriately monitored during therapy. If there is any deterioration of cardiovascular status, therapy should be stopped. Ribavirin should be administered with additional precautionary statement for diabetic patients and patients with history of gout to increase the safety of test drug administration

In addition, ribavirin is contraindicated in patients with a history of hypersensitivity to ribavirin.

# STATISTICAL considerations and ANALYtical plan

## Primary and Secondary Study Variables

### Primary Variable

The early virological response as measured by decline in HCV-RNA during the first 12 weeks of peginterferon alpha-2a and ribavirin therapy (especially the 1st and 2nd phase reduction in HCV RNA) in the three study arms.

### Secondary Efficacy Variables

### VRVR, RVR, cEVR, and pEVR rates defined as percentage of patients achieving these goals as measured by TaqMan PCR in the two three arms.

### Percentage of patients with non-detectable HCV-RNA at study day 1, 3, 7, 14, 21, 28, week 8, week 12, end of treatment, and 24 weeks after completion of treatment as measured by TaqMan PCR as compared to day 0.

### SVR rate defined as percentage of patients with non-detectable HCV-RNA as measured by TaqMan PCR at 24 weeks post completion of the treatment period in the three study arms.

### Relapse rates defined as percentage of patients with non-detectable HCV-RNA as measured by TaqMan PCR at the end-of-treatment but with detectable HCV-RNA 24 weeks post completion of the treatment period in the three study arms.

### SVR rate and percentage of patients with normal serum ALT levels at 24 weeks after completion of the treatment period in the total patient population, and its association with the following factors:

### early virological response

### pharmacokinetic response to ribavirin

### Secondary Safety Variables

- Adverse event rate and profile
- Other laboratory tests
- The proportion of patients experiencing anemia grade 1 (10.5-9.5 g/dL), grade 2 (9.4-8.0 g/dL), grade 3 (7.9-6.5 g/dL), and grade 4 (< 6.5 g/dL) will be evaluated in each study arm.

## Statistical and Analytical Methods

### Analysis Plan

This is a pilot trial with the viral kinetic response and SVR measured as described above, during the first 12 weeks of therapy as primary endpoint with the aim of investigating the feasibility and safety of “loading” and “priming” dosing of ribavirin in conjunction with PEG-IFN for chronic HCV genotyp 1. Intention-to-treat and Per-protocol analysis on primary endpoints will be performed for patients receiving at least one dose of the study drugs. Additionally, an analysis of SVR with regards to whether or not the target concentration of ribavirin 2.5 mg/L (10.25 μmol/L) at day 28 was achieved across all study arms will be performed.

#### Definition of Analysis Populations

**Intent-to-treat analysis population** is defined to include all patients who received at least one dose of study medication. Except for change from baseline parameters, the primary and all other secondary efficacy parameters will be analyzed using the intent-to-treat population.

**Per-protocol** **analysis population** is defined to include all patients who received ≥80% of both planned Pegasys and Copegus dose for ≥80% of planned treatment duration.

**Standard analysis (per-protocol) population** will exclude a patient if the patient meets any of the exclusion criteria listed in Section 9.2.2.2. Analysis using the standard population will be performed only if > 5% of patients are excluded from one of the treatment groups.

**Safety analysis population** is defined to include only patients who receive at least one dose of (either) study medication and have at least one post-baseline safety assessment.

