## Stopping Rule

Regardless of treatment arm, all patients achieving ≤ 2 log10 reduction in HCV RNA by week 12 or having detectable HCV RNA at week 24, will discontinue therapy and be considered as “non-responders” not having achieved SVR.

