#### Exclusion of Data from Analysis

The following patients will be excluded from the standard (per protocol) analysis:

1. Patients who never took any study medication.
2. Patients on PEGASYS® who received ≤80% of both planned PEGASYS®  and COPEGUS® dose for ≤80% of planned treatment duration.
3. Patients with no post-baseline HCV-RNA assessment.

The following patients will be excluded from the safety analysis:

1. Patients who never took any study medication.
2. Patients without any post-baseline safety assessment.

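### The per-protocol set drops adherent patients whom the futility rule stops for poor HCV-RNA response, and the protocol's two per-protocol definitions do not match

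*Protocol*

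**What the plan says.** Section 9.2.1 (Analysis Plan) states that "Intention-to-treat and Per-protocol analysis on primary endpoints will be performed". The primary variable is the HCV-RNA decline over the first 12 weeks (Sections 6.1 and 9.1.1). Sections 9.2.1 and 9.3 add SVR to that wording, while Sections 6.2 and 9.1.2 list SVR as secondary.

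Section 9.2.1.1 names two sets that both carry the per-protocol label:

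- The per-protocol population "is defined to include all patients who received ≥80% of both planned Pegasys and Copegus dose for ≥80% of planned treatment duration".
- The standard analysis (per-protocol) population is defined by exclusions. For this set, "Analysis using the standard population will be performed only if > 5% of patients are excluded from one of the treatment groups".

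The exclusions are in Section 9.2.1.2, although 9.2.1.1 points to a Section 9.2.2.2 that is not in the table of contents. The second exclusion covers "Patients on PEGASYS® who received ≤80% of both planned PEGASYS" and Copegus "dose for ≤80% of planned treatment duration". The third covers "Patients with no post-baseline HCV-RNA assessment", a condition that the first set lacks.

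The Treatment Duration section gives 24 weeks with RVR, 48 without, and possibly 72 for slow responders. Section 3.1 gives 28, 52 and 76 weeks in Group B, including priming. Under the Stopping Rule, patients with at most a 2 log10 "reduction in HCV RNA by week 12 or having detectable HCV RNA at week 24, will discontinue therapy" and count as SVR failures. Nothing says that such a stop completes planned treatment.

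**The concern.** A per-protocol set should hold patients who were treated as the protocol asks. Here a patient can take every dose, be stopped exactly as instructed, and be removed for it. The stop is triggered by a small fall in HCV RNA, and the fall in HCV RNA is the primary variable. Membership therefore depends on the outcome. If one arm works less well, it loses more poor responders and the surviving groups look more alike than they are.

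The criterion also looks past the endpoint. The primary variable is complete at week 12, but membership depends on exposure up to week 48 or 72. The synopsis plans an interim analysis of the primary endpoints once all patients reach week 12. If the per-protocol analysis is run then, the criterion cannot be evaluated for patients planned for 48 or 72 weeks.

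The two definitions admit different patients under the same label, so the choice between them could be made after the data are seen. The patient on whom they disagree is a realistic one, because ribavirin reduction for anaemia is permitted in all arms.

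**Working it through.** The protocol gives no figure for the size of the per-protocol set, so there is none to reproduce.

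**1. Exposure at a futility stop.** Share = weeks treated / planned weeks, compared with 80%. Durations are from the Treatment Duration section and Section 3.1.

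| Patient without RVR, fully dosed | Stop at week 12 | Stop at week 24 | 80% threshold |
|---|---|---|---|
| A and C, 48 weeks planned | 12/48 = 25% | 24/48 = 50% | 38.4 weeks |
| B, ribavirin, 52 weeks planned | 16/52 = 31% | 28/52 = 54% | 41.6 weeks |

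All four are below 80%, so every such patient fails the 9.2.1.1 rule.

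Under exclusion 2 of 9.2.1.2 the same patient is excluded if dose means cumulative dose (25%) and kept if it means dose level while on treatment (100%).

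**2. Do the two rules match?** Rule one includes a patient if peginterferon, ribavirin and duration are each at least 80%. Rule two excludes a patient only if all three are at most 80%. I set each of the three to 50%, 80% or 90%, which gives 27 combinations. The rules disagree in 13:

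- In 12 the patient fails rule one but is not excluded by rule two, for example 90% peginterferon, 50% ribavirin, 90% duration.
- In one (80% on all three) the patient is both included and excluded.

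**3. Size for the slope endpoint.** Means are from Section 9.3: day 0-3 decline 0.9 (C) and 1.4 (A) log10; slope 0.4 and 0.6 log10/week. No SD is given. Solving the two-means formula for 35 per arm, one-sided 5% and 80% power gives SD = difference x sqrt(35/2) / (1.645 + 0.842), that is 0.84 for the first phase and 0.34 for the slope. I also tried a slope SD of 0.20.

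Assume independent normal variables, and a week-12 decline equal to the first phase plus 11 weeks of slope. Its mean is 0.9 + 11 x 0.4 = 5.3 in C and 1.4 + 11 x 0.6 = 8.0 in A.

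- Slope SD 0.34: SD of the week-12 decline = sqrt(0.84² + (11 x 0.336)²) = 3.79. The share at or below 2 log10 is Φ((2 - 5.3)/3.79) = 19% in C and Φ((2 - 8.0)/3.79) = 6% in A. Among those kept, the slope difference falls from 0.20 to 0.13, or 35%.
- Slope SD 0.20: SD = sqrt(0.84² + (11 x 0.20)²) = 2.35. The shares are 8% and under 1%. The difference falls from 0.20 to 0.17, about 14%.

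Adding a detection floor of 15 IU/mL and a baseline of 5.5-6.5 log10 (simulation, 400,000 per arm) gives a reduction of 37-45% at SD 0.34 and about 13-15% at SD 0.20. Over variants of the model the range is roughly 12-45%. The week-24 stop is not modelled.

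**4. Size for SVR, if it is analysed per protocol.** Stopped patients are all failures, so the per-protocol rate = ITT rate / (1 - share stopped). All inputs here are assumed.

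- 30% stopped in C, 15% in A, SVR 40% and 55%: 0.40/0.70 = 57.1% and 0.55/0.85 = 64.7%. The 15-point difference becomes 7.6 points.
- 30% stopped in both arms: 0.55/0.70 = 78.6% against 57.1%. The difference becomes 21.4 points.

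The SVR distortion can therefore go either way. It shrinks the difference when the weaker arm has clearly more stops.

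**The case against.** The strongest defence is that planned treatment duration is already response-guided and cut short by a mandatory rule, so a stopped patient's plan could be read as ending at the stop. The term is indeed undefined for these patients. But the only durations the protocol gives are the fixed ones, and nothing supports the kinder reading.

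Second, this is a pilot, and ITT on the same endpoints keeps these patients. That stands and limits the harm. Section 9.2.1.1 does exempt change-from-baseline parameters from its ITT sentence, but 9.2.1 orders ITT on the primary endpoints and I take that as governing. However, 9.2.1 places per-protocol beside ITT without calling it supportive.

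Third, the direction is not guaranteed. Ribavirin reductions could also remove patients from the double-dose arm, which the calculation leaves out.

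A reader might infer more than the documents support:

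- *Every response rate is inflated.* Per-protocol analysis is planned only for primary endpoints. SVR is affected only under the wording of 9.2.1 and 9.3; the other response rates are secondary.
- *At least 14% would be removed.* The 86% week-12 response in Section 1.4.2 comes from another trial that included other genotypes. It sets no floor here.
- *The primary analysis cannot be run.* The synopsis calls the week-12 look an interim analysis and does not say that per-protocol is run then. At study end duration is known.
- *One section makes the analysis unconditional and another conditional.* The 5% trigger attaches only to the standard set, so the statements can coexist. The shared label is what confuses.

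**Conclusion.** The point holds. On the ordinary reading of planned duration, the 9.2.1.1 set removes fully adherent patients without RVR who are stopped at week 12 or 24 (25% or 50% of 48 weeks; 31% or 54% for Group B ribavirin) because of their HCV-RNA response. The per-protocol analysis of the primary endpoint then conditions on that endpoint. The mismatch between 9.2.1.1 and 9.2.1.2 follows from the text alone and needs no assumption.

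The size is uncertain. A loss of roughly 12-45% of the day 7-28 slope difference rests on slope SDs of 0.20-0.34, a first-phase SD of 0.84, a baseline of 5.5-6.5 log10 and normality, none of which the protocol states. Shrinkage is the likely direction if the weaker arm has more futility stops. ITT results are not touched, so this does not undermine the trial's main comparison. It makes the companion analysis misleading and its population ambiguous.

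**What to change.** Before data are seen, revise Sections 9.2.1.1 and 9.2.1.2:

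- Keep one per-protocol definition and make the exclusion list its exact complement, replacing exclusion 2. Say whether dose means cumulative dose, and correct the cross-reference.
- For the viral-kinetic primary endpoint, require at least 80% of each drug's planned dose over the primary window only: the first 12 weeks of peginterferon, plus the priming period in Group B. A fully dosed patient stopped at week 12 then has 12/12 = 100% and stays in. A window ending at day 28 would be too short for a 12-week variable.
- For any per-protocol SVR analysis, let planned duration end at a protocol-mandated futility stop. A fully dosed patient stopped at week 24 then has 24/24 = 100% and stays in as a non-responder.
- State whether the 5% trigger applies to this single set.
- Label per-protocol as supportive of ITT.

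The cost is definition text only. Treatment, visits and the stopping rule are unchanged. Per-protocol response rates will look slightly lower.
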